**Figure 1. Data collection visits in the experimental phases in the discontinuation study.**

*Data collection visits*

*Phase I*

- Visit I-0 – Commencement of Phase I for all subjects; Commencement of RS period for Group OKd (Experiment 1)
- Visits I-1, I-3, I-6, I-7: about one, three, six and seven months after Visit I-0

*Phase II*

- Visit I-7 – Commencement of Phase II for all subjects; Commencement of RS period for Group OKd (Experiment 1) and all subjects in Experiment 2
- Visits II-1, II-3, II-6, II-7: about one, three, six and seven months after Visit I-7

**Experiment 1.** *Discontinuation of lens wear in existing ortho-k children*

The objective of this study is to compare eyeball elongation in existing ortho-k subjects who stopped lens wear with subjects who continued ortho-k lens wear and control subjects wearing glasses.

Figure 1 shows the required visits for the duration of the experiment for each group of subjects.

In this experiment, subjects who have completed the ROMIO, TO-SEE and HM-PRO studies will be invited to participate. All spectacle-wearing control subjects will be invited to continue as control subjects. Ortho-k subjects will be randomly assigned into Groups OKc or OKd.

All subjects will be followed up for a period of 14 months.

- Group C will continue to wear spectacles for the duration of the experiment
- Group OKc will continue lens wear for the duration of the experiment
- Group OKd will be required to discontinue lens wear for 6 (+1*) months (and wear single-vision spectacles Phase I) and then resume ortho-k lens wear for another 6 (+1*) months (Phase II). *The first month (*) of each phase (See Figure 1), where indicated, is the RS (Refraction Stabilization) period to allow stabilization of refractive errors.*

*Group OKd*

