At the beginning of Phase I (Spectacle-wear phase), subjects will be required to wear single-vision spectacles to aid distance vision in the RS period. They are required to use their old spectacles which should be +/– 0.50DS in sphere and +/– 0.50 DC in cylinder from the refraction determined at the time of visit, otherwise, new spectacle lenses will be ordered. They will be followed up weekly until stabilization of refractive errors has been achieved and the stabilized refraction will be used for the prescription of the spectacles which will be delivered at Visit I-1. Once the refraction has stabilized, all children will be required to wear fully-corrected spectacles in the daytime during Phase I. They will be excluded if they regularly use any kind of contact lenses during Phase I.

New ortho-k lenses for these subjects will be ordered one month before the end of Phase I (ie. at Visit I-6) and dispensed at the end of Phase I (Visit I-7) before commencing Phase II (see Table 1).

In Phase II (Ortho-k phase), subjects are required to wear the ortho-k lenses every night unless otherwise instructed by their examiner. They need to attend the ortho-k aftercare visits as scheduled. Complimentary contact lens solutions and lens accessories (Table 2) will be supplied during the treatment. They have to keep an ortho-k journal everyday. Single-vision spectacles may be needed to aid distance vision during the RS period.

Cycloplegic data collection will be conducted at the beginning of each phase, at the end of RS period (for Group OKd only) and at the end of each phase. Subjects will be required to come back for the regular non-cycloplegic data collection visits after RS period. Change in axial length in the 6 months following stabilization of refractive errors for each Phase will be determined and compared within subjects and between groups. The whole study period for each subject will last for about 14 months.

*Group C and Group OKc*

Subjects will wear their habitual spectacles/ortho-k lenses at the commencement of Phase I, before Visit I-1. New glasses will be made based on Rx determined at Visit I-0 and delivery of new glasses will be at Visit I-1 and if indicated (based on data collected at Visit I-6), at Visit I-7 before commencing Phase II. Note that there is no RS period for these two groups of subjects, but cycloplegic and non-cycloplegic data correction visits will be same as Group OKd.

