**Experiment 2.** *Discontinuation of lens wear in new ortho-k children*

The objective of this experiment is to compare axial elongation in younger and older children during ortho-k treatment and after discontinuation of ortho-k lens wear. Forty-five children (aged 6-10) and 45 older children (aged 11-15) who are myopic of 1.50 to 4.50D and who intend to have overnight ortho-k for myopic control will be recruited via advertisement in newspaper or by referral. They should have no previous experience in rigid lens wear and no prior experience in myopic control treatment. The inclusion criteria are listed in Table 3.

Similar to Experiment 1, the subjects will have to participate in a two-phase experiment (see Figure 1).

At the commencement of Phase I (Visit I-0), the subjects’ baseline data will be collected and prescriptions for new spectacles will be determined. New spectacles will be dispensed at Visit I-1. They will be required to use the spectacles in the daytime for the following 6 months (the rest of Phase I). Ortho-k lenses (Menicon Z Night or Menicon Z Night Toric) will be ordered 1 month before the end of Phase I (i.e. Visit I-6), after they have learnt lens handling. Ortho-k lenses, contact lens solutions and daily log will be dispensed at the end of Phase I (Visit I-7) before commencing Phase II (see Table 1). They are required to wear the ortho-k lenses every night in Phase II unless otherwise instructed by their examiner.

Visits schedule and methodology will be the same Experiment 1 (Figure 1 & Table 1).

The study period for each subject will be about 14 months (including 1 month for baseline data collection).

**Experiment 3.** Refractive and corneal changes, including corneal thickness, corneal hysteresis, and corneal resistant factor during ortho-k treatment and the discontinuation of the treatment will be determined. These will be compared in new and existing ortho-k subjects and children of different ages. Information will be collected from subjects participating Experiments 1 and 2.

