- The first overnight visit. The following morning after commencing lens wear. It is within 2 hours after waking and children should wear the lenses to our clinic.
- One week aftercare visit. Seven days ( 3 days) after commencing lens wear, 2 hours after waking.
- Two weeks aftercare visit. Fourteen days ( 3 days) after commencing lens wear, 2 hours after waking.
- Three weeks aftercare visit. Twenty-one days ( 3 days) after commencing lens wear, 2 hours after waking.
- One month aftercare visit. Twenty-eight days ( 3 days) after commencing lens wear. Can be in the morning or in the afternoon.
- The three monthly after care visits. It will coincide with the data collection visits.

*Visits during RS period (Group OKd in Experiment 1 and all subjects in Phase II in Experiment 2)*

Weekly ( 3 days) review of refraction, corneal shape and ocular conditions once the ortho-k treatment has stopped. It usually consists of 4-6 visits, depending on the initial refractive errors of the subjects. Refraction is considered stabilized when the change in refractive sphere and refractive cylinder in manifest refraction in two consecutive visits is 0.25 D or less and cycloplegic examination (cycloplegic data collection visit at end of RS period) will be arranged in the following week.

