***Study period***

Experiments 1 and 2 can commence at the same time. For Experiment 1, each subject will be followed for 14 months. Subjects in the 2-year myopic control studies will be returning for their final visit in the next 12 months. Assuming that the subjects required in Experiment 1 can be recruited in 12 months and 2 months to complete data collection, the study period will be at least 28 months (12+14+2).

For Experiment 2, each subject will be followed for 13 months. Assuming 6 months for subject recruitment, and 2 months for data collection, the study period will be 22 months (6+14+2). As the two experiments can be conducted concurrently, and allowing for delays (eg delays in recruitment or subject returning for data collection), the estimated study period will be at least 28 months (Table 5).

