**Table 1. Data collection visits for Experiments 1 & 2.**

| Cycloplegic | Non-cycloplegic | Description | Remark |
| --- | --- | --- | --- |
| Phase I |  |  |  |
| I-0 |  | Baseline |  |
| [RS period: Weekly visits (for Group OKd subjects) to determine stabilization of Rx. Order new ortho-k/spectacles for the 3 groups of subjects for delivery at Visit I-1 (Rx for Group C and OKc should not be more than 1 month old)] | | | |
| I-1 |  | End of RS period in Phase I (3 days)  (*same visit as I-0 for Experiment 2 as there will be no RS period) | - Delivery of glasses for Group C and ortho-k lenses for Group OKc - Delivery of glasses for Group OKd and all subjects in Experiment 2 |
|  | I-3 | 3 (1 week) after commencing Phase I |  |
|  | I-6 | 6 months (1 week) after commencing Phase I | - Order new ortho-k lenses/spectacles based on updated Rx for the 3 groups of subjects for Visit I-7 where indicated |
| I-7 |  | 7 months (1 week) after commencing Phase I |  |
| Phase II |  |  |  |
| II-0 |  | Equivalent to Visit I-7 | - Glasses for Group C and ortho-k lenses for Group OKc (if deemed necessary) - Ortho-k lenses for Group OKd and all subjects in Experiment 2 |
| II-1 |  | End of RS period (3 days) |  |
|  | II-3 | 3 (1 week) after commencing Phase II |  |
|  | II-6 | 6 months (1 week) after commencing Phase II |  |
| II-7 |  | 7 months (1 week) after commencing Phase II |  |

RS - Rx-Stabilization

Group C – Control group in Experiment 1

Group OKc – Ortho-k subjects who will continue ortho-k lens wear for the whole experiment period in Experiment 1

Group OKd – Ortho-k subjects who will discontinue ortho-k lens wear in Phase I and resume ortho-k lens wear in Phase II in Experiment 1

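### The 6-month axial length change is taken over windows of unequal length, because the start visit moves with stabilization, the end visit is fixed, and the rules for Visit I-1 conflict

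*Protocol*

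**What the plan says.** Axial length is the primary outcome. The Group OKd text under Experiment 1 states the comparison: "Change in axial length in the 6 months following stabilization of refractive errors for each Phase will be determined and compared", both within subjects and between groups. Experiment 2 is said to follow the visit schedule and methodology of Experiment 1.

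The end of the window is fixed by the calendar. The visit list under Figure 1, the Examination procedures and Table 1 all place I-7 and II-7 seven months after the phase begins.

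The start of the window has more than one rule:

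- The list under Figure 1 places Visits I-1, I-3, I-6 and I-7 "about one, three, six and seven months after Visit I-0", with no exception for any group or experiment.
- The Examination procedures tie the end-of-RS cycloplegic visit to one week after refraction has stabilized, for Group OKd in both phases and for Experiment 2 in Phase II. Of the weekly RS reviews they say: "It usually consists of 4-6 visits, depending on the initial refractive errors of the subjects".
- For Experiment 2, Table 1 describes I-1 as the "same visit as I-0 for Experiment 2 as there will be no RS period". The Experiment 2 text says: "New spectacles will be dispensed at Visit I-1. They will be required to use the spectacles in the daytime for the following 6 months", and treats those 6 months as the remainder of Phase I.
- For Experiment 1, the Group OKd text schedules cycloplegic measurement at the start of each phase, "at the end of RS period (for Group OKd only) and at the end of each phase". The next paragraph, on Groups C and OKc, says that their "cycloplegic and non-cycloplegic data correction visits will be same as Group OKd".

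The Study period section states: "For Experiment 2, each subject will be followed for 13 months". The Experiment 2 text gives about 14 months.

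**The concern.** A raw change grows with the time over which it is measured. If one group or phase is observed for longer than another, the difference in change contains a part that is due only to time, and a larger sample does not remove it.

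In Experiment 1, a short Group OKd window in Phase I would understate elongation after lenses are stopped, which is what the experiment is meant to detect. In Phase II it would understate elongation on resumed lenses. In Experiment 2, a spectacle window longer than the ortho-k window would make ortho-k look better than it is.

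**Working it through.** **The plan's own figure.** The Subject number section gives a difference of 0.12 mm, SD 0.17 mm, alpha 0.05 and 80% power. The normal formula, n = 2(1.960 + 0.842)² × (0.17/0.12)², gives 31.5, so 32. The two-sample t-test gives 32.5, so 33 per group. The stated 33 reproduces (two-sided) and is not in dispute. It supplies the yardstick: 0.12 mm over 12 months is 0.06 mm over 6 months if growth is linear.

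**Window lengths.** One month = 365.25/12/7 = 4.348 weeks, so 7 months = 30.44 weeks and 6 months = 26.09 weeks. Window = 30.44 minus the week of the start visit.

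Start visit under the stabilization rule: 4 to 6 weekly reviews plus one week. If the first review is counted at day 0, the start visit falls at weeks 4 to 6; if it is counted a week later, at weeks 5 to 7. Both counts are compatible with the text.

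| Start visit | Window (weeks) | Against 26.09 |
| --- | --- | --- |
| One month (C and OKc) | 26.09 | 0 |
| Week 4 | 26.44 | 1.3% longer |
| Week 5 | 25.44 | 2.5% shorter |
| Week 6 | 24.44 | 6.3% shorter |
| Week 7 | 23.44 | 10.2% shorter |
| Same as I-0 (Experiment 2 Phase I, Table 1) | 30.44 | 16.7% longer |

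**Size in millimetres.** The protocol gives no growth rate, so 0.20 to 0.36 mm/year is an assumption. One year is 52.18 weeks.

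- Week 7 shortfall: 26.09 − 23.44 = 2.65 weeks. 0.20 × 2.65/52.18 = 0.010 mm; 0.36 × 2.65/52.18 = 0.018 mm. Against 0.06 mm this is 17% to 30%. At week 4 there is no shortfall.
- One extra month in Experiment 2 Phase I: 0.20/12 = 0.017 mm; 0.36/12 = 0.030 mm, or 28% to 50% of 0.06 mm.
- With a wider assumption of 0.1 to 0.4 mm/year, the two figures become 0.005 to 0.020 mm and 0.008 to 0.033 mm.

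**Two further sources of variation, not in these ranges.** The tolerance on the end visits in Table 1, read as one week either way, adds about 0.23 month of scatter but applies to all groups alike. In Phase II, lens wear may begin up to 14 days after the last data collection visit while II-7 is timed from I-7. A week 7 start visit could then fall at week 9, leaving 30.44 − 9 = 21.4 weeks.

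**The case against.** The strongest reply concerns Experiment 2. The Objectives frame it in terms of rates, and a rate is already scaled by time, so a 7-month window against a 6-month one would not by itself create a treatment effect. An analysis plan that is not shown may say exactly that. The 7-month window also rests on one parenthesis in Table 1, against the Figure 1 schedule, the visit list below it and the Experiment 2 text. This stands as far as it goes: a reader might infer that Experiment 2 is biased by a month of growth, but that needs both Table 1 to govern and the change to be left unscaled. It does not settle the matter, because the only stated definition of the outcome is a raw change and Experiment 2 adopts the methodology of Experiment 1.

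For Experiment 1, the reply is that the mismatch may be nil. The protocol calls the RS period the first month of a phase, and a start visit at week 4 leaves no shortfall. That also stands: 10% is an upper end that would need every Group OKd child at week 7.

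Three other inferences are tempting and not supported:

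- That the window is shorter in higher myopes. The text says that the number of RS visits depends on initial refractive error, but gives no direction.
- That Groups C and OKc have no cycloplegic start measurement. The paragraph on those groups says that their visits match those of Group OKd, and Table 1 lists I-1 and II-1 as cycloplegic without exempting them. What remains is wording that conflicts.
- That Experiment 2 follow-up is really 13 months. The same section uses 14 in its own sum (6+14+2).

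**Conclusion.** The point holds in a limited form. The protocol promises a change over 6 months, compared within subjects and between groups, and its visit rules do not deliver equal windows. For Group OKd, and for Experiment 2 in Phase II, the window runs from about 26.4 down to 23.4 weeks against 26.1 weeks for a one-month start visit. At the assumed growth rates, the shortfall is worth from nothing to 0.010–0.018 mm, against 0.06 mm. In Experiment 2, the protocol contradicts itself on when I-1 takes place; the cost of 0.017 to 0.030 mm per extra month is conditional on Table 1 being followed and the change not being scaled.

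These sizes rest on linear growth, the assumed rates, Groups C and OKc attending at one month, and the counting of RS visits shown above. The conflicts between sections rest on no assumption. The sample size is unaffected.

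**What to change.** Define the outcome in both experiments, and in every group, as axial elongation per unit of actual elapsed time between the start and end cycloplegic visits of each phase, or as a slope on actual days. This removes the part of any difference that is due to window length, provided growth is close to linear over the window.

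Reconcile the following places:

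- Figure 1 and the visit list below it, the Experiment 1 and Experiment 2 texts, the Examination procedures and Table 1, on the timing of I-1 and II-1.
- The Group OKd paragraph and the Group C and Group OKc paragraph, on whether Groups C and OKc have cycloplegic axial length at I-1 and II-1.
- The Experiment 2 text and the Study period section, on 14 against 13 months.

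Which schedule is intended is for the sponsor to state. The cost is minor wording and analysis work. The scaling needs only the dates of the visits.

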***Subjects***

Children between 6-15 years old will be recruited. Informed consent will be obtained from both the parents and the children at the beginning of the study.

- For Experiment 1, 80 ortho-k and 40 control subjects who have completed the 2-year myopic control studies (ROMIO, TO-SEE & HM-PRO) will be recruited. They were 6-12 years old when they joined the myopic control study and will be 8-14 years old when they commence this part of the study. Ortho-k subjects will be randomized into Group OKc where subjects will continue lens wear for another 12 months and Group OKd where subjects will be required to cease lens wear for 6 (+1*) months and wear single-vision spectacles and then resume ortho-k lens wear for another 6 (+1*) months.
- In Experiment 2, two groups of 45 children of aged 6-11 and 12-15 years old, myopia of at least 1.50D and astigmatism of at most 2.50D, and who intend to have overnight ortho-k for myopic control and have no contra-indication for ortho-k lens wear will be recruited via advertisement in newspaper or by referral. Subjects will be monitored for 6 months before they are fitted with ortho-k lenses which they have to wear for 6 (+1*) months.

***Examiners***

One examiner (E1) will be responsible for lens fitting and monitoring the subjects and will therefore be involved in every visit. The masked examiner (E2) will be responsible for collection of the primary outcome measures, will be masked to the treatment received by each subject, and will only be involved in the data collection visits. Data entries and analysis will be made by another independent examiner (E3). E1 will also be masked to the AL measurements of each subject.

***Examination procedures***

Table 4a and 4b list the test procedures and instruments used respectively in this study.

*Experiment 1*

The examiners will perform all test procedures including

- subjective
- objective refraction
- high/low contrast logMAR visual acuity assessment
- corneal topography
- slit-lamp biomicroscopy
- axial length measurement** (Cycloplegic and non-cycloplegic examination)
- corneal pachymetry
- non-contact intraocular pressure measurement
- corneal biomechanics assessment
- peripheral refraction (10° and 20°) (Cycloplegic examination)
- aberration (Cycloplegic examination)

Cycloplegia will be used on each subject at the cycloplegic data collection visits (0.5% alcaine followed by 1% tropicamide and 1% cyclopentolate).

**Only the masked examiner performs axial length measurements. Masked examiner will NOT perform any other procedures.

*Experiment 2*

Same as Experiment 1.

*Data collection visits*

Primary outcome measures will be determined in these visits, i.e. axial length. There are two types of data collection visits – cycloplegic data collection visits and non-cycloplegic data collection visits. The cycloplegic data collection visits are performed at the baseline, at end of the RS period, and 7 months after the beginning of each phase (see Figure 1 and Table 1). The cycloplegic data collection visit at the end of RS period will be conducted one week after stabilization of refraction has been achieved for OKd subjects in both Phases I and II in Experiment 1 and all ortho-k subjects in Phase II of Experiment 2.

The non-cycloplegic data collection visits are conducted every 2-3 months after RS period. In order to minimize the effect of diurnal variation, the data collection visits will be scheduled at about the same time of the day for each visit.

*Ortho-k aftercare visits*

For ortho-k subjects only. Regular ortho-k aftercare visits will be arranged upon delivery of ortho-k lens wear to ensure healthy and safe ortho-k lens wear. The ortho-k effect will be reviewed one night, one week, two weeks, three weeks, one month, and every 2-3 months after commencing lens wear. The weekly visits in the first month will only apply during the RS period.

- Commencement of lens wear. The night when the ortho-k treatment commenced/resumed. It shall be within 14 days after the last data collection visit.
- The first overnight visit. The following morning after commencing lens wear. It is within 2 hours after waking and children should wear the lenses to our clinic.
- One week aftercare visit. Seven days ( 3 days) after commencing lens wear, 2 hours after waking.
- Two weeks aftercare visit. Fourteen days ( 3 days) after commencing lens wear, 2 hours after waking.
- Three weeks aftercare visit. Twenty-one days ( 3 days) after commencing lens wear, 2 hours after waking.
- One month aftercare visit. Twenty-eight days ( 3 days) after commencing lens wear. Can be in the morning or in the afternoon.
- The three monthly after care visits. It will coincide with the data collection visits.

*Visits during RS period (Group OKd in Experiment 1 and all subjects in Phase II in Experiment 2)*

Weekly ( 3 days) review of refraction, corneal shape and ocular conditions once the ortho-k treatment has stopped. It usually consists of 4-6 visits, depending on the initial refractive errors of the subjects. Refraction is considered stabilized when the change in refractive sphere and refractive cylinder in manifest refraction in two consecutive visits is 0.25 D or less and cycloplegic examination (cycloplegic data collection visit at end of RS period) will be arranged in the following week.

***Ortho-k lenses, solutions and spectacles lenses***

*Ortho-k lenses*

Menicon Z Night and Night Toric lenses will be used in this study. Lenses to be ordered will be determined by the Easy Fit software (based on topographic data captured by the Medmont corneal topographer, the manifest refractive error and the corneal diameter). Full correction will be attempted for myopia ≤ 4.50D and partial correction targeted for 4.00D will be applied for myopia  4.50D.

- All ortho-k subjects who agreed to be randomized in Experiment 1 and all subjects in Experiment 2 will be provided with the required ortho-k lenses during the study period(s) as indicated.
- Subjects who refused to be randomized into Group OKd can participate in DOEE study as subjects in Group OKc if they pay for the lenses used during the experimental period (these will not be complimentary lenses but will be ordered via our clinic, ie. payment of lenses will go to our Optometry Clinic). They have to agree to return for the scheduled aftercare and data collection visits and each subject will receive a pair of complimentary lenses at the end of the study period.

*Contact lens solutions & accessories*

All the solutions used in this study are shown in Table 2. All solutions have to be replaced at least once every 2 months.

- Group OKc – Subjects will be required to purchase all solutions required (except for O2 Care) from our Clinic
- Group OKd in Experiment 1 and all ortho-k subjects in Experiment 2 –Complimentary contact lens solutions will be provided
- All subjects will be given complimentary flat lens cases, SP vial for weekly protein removal and O2 Care daily cleaning during the study period.

*Spectacle lenses*

Spectacles are required during the discontinuation period and may be needed in the first 2 weeks of the lens wear period. Subjects will be asked to keep their habitual spectacles. Complimentary spectacles lenses will be provided if indicated, provided that subjects use their own frames. New spectacle lenses will be prescribed once the refraction has stabilized during the RS period (where appropriate). Low refractive index *spherical* lenses will be prescribed for low myopes (myopia < 4.50D) and high refractive index lenses will be used for high myopes ( 4.50D) and high astigmatism ( 2.00DC).

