***Objectives***

* The primary objectives of this study will be to compare

- eyeball elongation in existing ortho-k subjects who stopped lens wear with subjects who continued ortho-k lens wear and control subjects wearing glasses (Experiment 1)
- rates of change in axial length in younger and older myopic children when corrected with ortho-k and when ortho-k was discontinued (Experiment 2)
- rates of change in axial length in children with faster and slower myopic progression rates (Experiment 2)
- change in corneal parameters during and after discontinuation of lens wear (Experiment 3)

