***Subject number***

From the current ROMIO study, the mean different and SD of the change in axial length in the ortho-k and the control groups who have completed the 12-month lens wear timeline are 0.12 and 0.17mm respectively. To detect a 0.12mm (equivalent to 0.33D) between-group difference for an alpha value of 0.05 and 80% power in 12 months, a sample size of 33 is required for each group.

For Experiment 1, we aim to have at least 66 ortho-k and 33 control subjects completing this study. Allowing for about 15% dropout, we will recruit 80 ortho-k and 40 control children.

*The ROMIO, HM-PRO and TO-SEE studies are ortho-k projects currently being conducted in PolyU. ROMIO and HM-PRO studies are targeting 30 ortho-k and 30 control subjects each and TO-SEE study is targeting for 30 ortho-k subjects. Hence, there will be 90 potential ortho-k and 60 control subjects and so we do not expect difficulties in recruiting the required subjects for this experiment*.

For Experiment 2, we aim to have at least 70 (35 younger and 35 older) subjects completing the study. Allowing for dropouts (including unsuccessful lens wear), we will recruit 90 (45 younger and 45 older) children.

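### Group OKc as defined mixes randomised children with children who refused randomisation, which opens the OKd versus OKc comparison to selection bias of unknown size and direction

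*Protocol*

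**What the plan says.** The Experiment 1 description states the allocation without exception: "Ortho-k subjects will be randomly assigned into Groups OKc or OKd". The Subjects section repeats it: "Ortho-k subjects will be randomized into Group OKc where subjects will continue lens wear for another 12 months", with Group OKd as the alternative.

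The section on ortho-k lenses, solutions and spectacle lenses then sets a further rule: "Subjects who refused to be randomized into Group OKd can participate in DOEE study as subjects in Group OKc". The condition is "if they pay for the lenses used during the experimental period". They must also agree to attend the scheduled visits, and "each subject will receive a pair of complimentary lenses at the end of the study period". Children who accept randomisation are treated differently on supply: "All ortho-k subjects who agreed to be randomized in Experiment 1 and all subjects in Experiment 2 will be provided with the required ortho-k lenses".

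The comparison concerned is in the first primary objective: "eyeball elongation in existing ortho-k subjects who stopped lens wear with subjects who continued ortho-k lens wear and control subjects wearing glasses". On numbers, the Subject number section says "we aim to have at least 66 ortho-k and 33 control subjects completing this study", from 80 ortho-k and 40 control recruits. It does not say whether a child who refused randomisation counts toward the 80 or the 66. The legend to Table 1 defines OKc only by continued lens wear, and a refuser meets that definition in full.

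**The concern.** Two sections make OKc and OKd the arms of a randomised comparison, and a third fills one of those arms partly by family choice. A refuser can enter OKc but never OKd. Refusers must also be willing to pay for lenses that randomised children receive free. Preference, means and past response to lens wear may therefore differ between the groups for reasons unrelated to allocation.

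The spectacle controls are carried over from earlier studies, so OKd versus OKc is the only between-group contrast in Experiment 1 that randomisation protects. If refusers are analysed under their group label, that protection is weakened.

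The wording of the rule adds a second risk. Refusing randomisation into OKd can be read as declining before allocation, or as declining once OKd has been drawn. The second reading would let a child allocated to stop lens wear be relabelled as continuing.

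**Working it through.** **1. The plan's own sample size.** Inputs from Subject number: difference 0.12 mm, SD 0.17 mm, alpha 0.05 (taken as two-sided, which reproduces the figure) and power 80%. The standardised difference is 0.12/0.17 = 0.706. A two-sample t-test needs 32.5 per group, rounded up to 33, and power at 33 per group is 80.6%. The stated 33 is reproduced. For dropout, 66/0.85 = 77.6, so 80 ortho-k recruits is adequate. The sample-size arithmetic is not at fault.

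**2. Share of OKc that is self-selected (s).** The protocol gives no refusal rate, so both readings of the 80 are shown.

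- *All 80 are randomised, with refusers on top.* The Subject number section counts 90 potential ortho-k children, so at most 90 − 80 = 10 can be refusers. Then s is at most 10/(40 + 10) = 20%.
- *Refusers count within the 80.* With assumed refusal fraction f, each randomised arm has 80(1 − f)/2 children, OKc has that number plus 80f, and s = 80f/(80f + 40(1 − f)).

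| f (assumed) | Refusers | Randomised per arm | Total in OKc | s |
| --- | --- | --- | --- | --- |
| 10% | 8 | 36 | 44 | 18% |
| 20% | 16 | 32 | 48 | 33% |
| 30% | 24 | 28 | 52 | 46% |

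**3. Bias.** If refusers' mean elongation differs by d from that of randomised OKc children, the OKc mean, and so the contrast, shifts by s × d. Take d = 0.03 to 0.06 mm. This is an assumption with no source in the protocol, and its sign is unknown.

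- s = 20% (the cap if all 80 are randomised): 0.006 to 0.012 mm, or 5–10% of 0.12 mm.
- s = 18%: 0.005 to 0.011 mm.
- s = 33%: 0.010 to 0.020 mm.
- s = 46%: 0.014 to 0.028 mm.

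Over s = 18–46% the shift is about 0.005–0.03 mm, up to roughly a quarter of the planning difference.

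**4. Power, pooled and randomised-only.** This uses refusers within the 80, 15% dropout in every group, and a two-sample t-test at 0.12/0.17 mm.

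| f (assumed) | Completers OKd v pooled OKc | Power, pooled | Completers per randomised arm | Power, randomised only |
| --- | --- | --- | --- | --- |
| 10% | 30.6 v 37.4 | 81.4% | 30.6 | 78% |
| 20% | 27.2 v 40.8 | 80.2% | 27.2 | 72% |
| 30% | 23.8 v 44.2 | 78.1% | 23.8 | 66% |

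Pooling leaves nominal power near the planned level; its harm is bias. The lower figures in the last column are what it costs to restore a randomised comparison if refusers occupy places among the 80.

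**The case against.** Following refusers on their preferred treatment is a recognised recruitment option. These children can be identified, because they pay through the clinic while randomised children are supplied. The choice of analysis set is commonly left to the analysis plan, which is not shown and might keep refusers apart. The rule also stands in a section about lens supply. All of this is fair, and it means the defect can be corrected. It does not remove the conflict: group membership is an allocation rule that the protocol itself sets, and it gives refusers the same group label with no separate code.

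A reader might infer any of four stronger conclusions, and the protocol supports none of them.

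- *OKd versus OKc is no longer randomised at all.* Children who accept randomisation remain a valid randomised subset.
- *Pooling costs the trial its power.* It does not: pooled power stays at about 78–81%.
- *Refusers are good compliers or slow progressors, so the direction of bias is known.* Nothing in the protocol says so. Families worried about fast progression could equally refuse to stop. The rule that non-compliant children in any group are asked to withdraw also narrows a difference in compliance.
- *All of Experiment 1 is compromised.* OKd versus spectacle controls, and the comparison of phases within OKd, do not involve refusers.

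The Subjects section can also be read as meaning that all 80 are randomised. On that reading the self-selected share is at most about 20%, and the larger shares do not apply.

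**Conclusion.** The point holds for the groups as the protocol defines them. The Experiment 1 and Subjects sections randomise ortho-k children without exception, and the lens-supply section adds self-selected children to one arm of a primary comparison. Followed as written, OKd versus OKc is exposed to selection bias whose size and direction cannot be determined from the protocol.

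The illustrative shift of about 0.005–0.03 mm rests on an assumed refusal rate of 10–30% and an assumed difference of 0.03–0.06 mm of either sign; it is not an estimate. The conflict between the sections does not depend on those assumptions. It should be settled before enrolment, because a refuser not coded apart at entry may be hard to separate later.

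**What to change.** Reconcile the Experiment 1, Subjects, lens-supply and Subject number sections as follows.

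1. Let refusers take part under a separate non-randomised code, for example OKc-N, and report them descriptively.
2. Record agreement to randomisation before allocation is revealed, so that a child allocated to OKd cannot be relabelled OKc.
3. Base OKd versus OKc on randomised children as allocated.
4. State that only randomised children count toward the 33 completers per arm, and say whether the 80 includes refusers.

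The cost is a change of wording, one group code and a smaller OKc group in the main comparison. If all 80 are randomised, the planned power stands, but the pool of 90 leaves room for only 10 refusers or non-participants. If refusers are counted within the 80, the stated 80% must be replaced by the randomised-only figure: about 78%, 72% or 66% at 10%, 20% or 30% refusal with 15% dropout.
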